### 3.2.4 ADDITIONAL ENDPOINTS OF THE CORE STUDY AND LTE OBSERVATIONAL PERIOD

1. Immunologic changes (pharmacodynamics) following daratumumab treatment will be evaluated as follows:

- Change from baseline in number and phenotype of peripheral blood plasmacytoid dendritic cells (pDC), natural killer (NK) cells, CD4+ and CD8+ T cells, CD19+ B cells and CD19+CD20negCD27high plasmablasts, by visit. Immunophenotyping will be performed by multicolor flow cytometry including expression analysis of CD38 on immune cell subsets by using an anti-CD38 multipeptide antibody that binds to an epitope distinct from the epitope bound by daratumumab. Time frame: baseline, and follow-up visits of the core study period at Week 3, 5, 7, 9, 12, 16, 20, 24, 28, 32, 36, and at Week 42, 48, 54, 60, 66, 72, 78 and 84 of the LTE observational period.
- Change from baseline in interferon type I activity, by visit, Time frame: up to Week 36. Type I interferon activity is a hallmark of SLE; it will be measured by analyzing its surrogate parameter SIGLEC-1 (CD169) on monocytes by flow cytometry. Time frame: baseline, and follow-up visits of the core study period at Week 3, 5, 7, 9, 12, 16, 20, 24, 28, 32, 36, and at Week 42, 48, 54, 60, 66, 72, 78 and 84 of the LTE observational period.  
Change from baseline in gene expression profile and antigen receptor repertoire on peripheral blood T and B cells. Time frame: week 9 (one week after the last daratumumab injection). Transcriptomic profiling will be performed using single-cell RNA sequencing (scRNA-Seq) combined with T cell receptor (TCR) and B cell receptor (BCR) analysis in peripheral blood CD4+ and CD8+ T cell and CD19+ B cell subsets. Time frame: baseline and follow-up visit of the core study period at Week 9, and at the entry visit in the LTE observational period.

2. Pharmacokinetics will be investigated as follows:

- Daratumumab concentrations will be analyzed after the end of the study from cryopreserved serum samples, which had been obtained at Week 9 (one week after the last daratumumab injection), provided that the primary endpoint will be achieved. Time frame: Week 9 of the core study, and at entry visit in the LTE observational period.

## 3.3 HYPOTHESIS

Plasma cells not only provide protective humoral immunity, they are also implicated in the pathogenesis of SLE and other autoantibody-mediated diseases. CD38 is a transmembrane glycoprotein with ectoenzymatic functions located predominately at the surface of plasma cells, making it an attractive target for novel plasma cell directed therapies [25]. Anti-CD38 monoclonal antibodies, such as daratumumab, have been previously demonstrated to induce a substantial depletion of plasma cells in the bone marrow of patients with refractory multiple myeloma, and are currently used in clinical practice [53]. In SLE, pathogenic autoantibodies are secreted by short- and

long-lived plasma cells, the latter being refractory to conventional and B cell depleting therapies. The hypothesis is that depleting plasma cells with daratumumab in SLE will result in a significant decrease of serum anti-dsDNA autoantibody levels, leading to clinical improvement. This notion is supported by recent positive reports on a therapeutically relevant depletion of plasma cells in two refractory SLE patients [52] and other autoimmune diseases [47-49]. Previously published data of the sponsor demonstrated that CD38 expression is significantly increased on peripheral blood plasma cells compared to those from healthy controls [52]. In addition, daratumumab effectively depleted plasma cells isolated from peripheral blood of SLE patients *ex vivo* and induced a down regulation of CD38 on remaining plasma cells similar to healthy controls [57]. It is, therefore, reasonable to hypothesize that CD38 could be a potential therapeutic target for the treatment of systemic autoimmune diseases by specifically depleting antibody-producing plasma cells. Given the high unmet need for efficacious disease-modifying treatment in such diseases, studies are warranted to determine whether and how anti-CD38 antibody-based therapies may delay or prevent the disease progression of systemic autoimmune diseases [58].

## 4 TRIAL DESIGN

### 4.1 STUDY SETTING

This is a phase 2 monocenter, open label, Proof-of-Concept (PoC) study. A target of 10 participants with moderate to severe SLE will be enrolled in the study.

Screening Period: 28 days

Treatment Period: 8 weeks

Study type: interventional, open-label, uncontrolled

### 4.2 OVERVIEW OF STUDY DESIGN

After a screening period of 4 weeks, the following visits are planned in the core study period:

[figure not shown]

The long-term extension observational period includes a total of 8 follow-up visits every 6 weeks as follows:

[figure not shown]

### 4.3 STUDY POPULATION

In this study, the target population is participants with SLE according to EULAR/ACR 2019 classification criteria [7] with moderate to severe disease, reflected by a Systemic Lupus Erythematosus Disease Activity Index 2000 (SLEDAI-2K) score  $\geq 6$  [12], despite conventional treatment (e.g. immunosuppressants, antimalarial drugs, corticosteroids) and failure of achieving remission or lack of tolerability with at least two prior disease modifying anti-rheumatic drugs. There is a positive correlation between serum anti-dsDNA autoantibodies and the number of circulating blood CD38+ plasma cells in SLE [20]. Therefore, participants must have increased serum levels of anti-dsDNA autoantibody titers observed during screening.

### 4.4 STUDY PHASE/PERIODS, TREATMENT GROUP

Treatment period: 8 weeks

Primary endpoint: at Week 12

Follow-Up period of core study period: 28 weeks

Total study duration per subject in core study period: 40 weeks (4 weeks screening, 8 weeks treatment, 28 weeks follow-up)

Study duration of the LTE observational period: 48 weeks (8 follow-up study visits every 6 weeks)

First patient first visit to last patient first visit: 15 months

Total study duration of the core study period: 24 months

Total study duration: 88 weeks (40 weeks core study period and 48 weeks LTE observational period)

Interim analysis: after the 5th patient at Week 12

### 4.5 PATIENT REPORTED OUTCOMES

Incorporating disease-specific health-related QoL measures as endpoints is important in providing patient-centric care to improve outcomes pertinent to patients with SLE. The following scores will be used to assess the quality of life in this study:

- medical outcomes study Short-Form 36 (SF36)
- Functional Assessment of Chronic Illness Therapy-Fatigue (FACIT-Fatigue)

## 5 PATIENT ELIGIBILITY

All screening evaluations that determine subject eligibility will be performed and reviewed by the investigator before a subject can be included into the study. It is permitted to rescreen patients.

## 5.1 INCLUSION CRITERIA OF THE CORE STUDY PERIOD

Each potential participant must satisfy all the following criteria to be enrolled in the study:

1. diagnosis of SLE according to the 2019 EULAR/ACR Systemic Lupus Erythematosus classification criteria.
2. age between 18 and 60 years, inclusive, at consent.
3. have a body mass index (BMI) between 18 and 32 kg/m^2 (BMI = weight/height), inclusive, and a body weight of no less than 35 kg.
4. demonstrate moderate to severe disease based on SLEDAI-2K score  $\geq 6$  observed at screening
5. SLEDAI-2K  $\geq 4$  for clinical features (i.e. SLEDAI excluding laboratory results) at screening
6. have a positive anti-double stranded deoxyribonucleic acid (anti-dsDNA) test, as measured by enzyme-linked immunosorbent assay (ELISA) test.
7. Failure or lack of tolerability of at least 2 previous state-of-the-art immunosuppressive drugs/immunomodulatory drugs including antimalarials (does not account for glucocorticoids).
8. if using oral corticosteroids, must be receiving this medication for at least 4 weeks and on a stable dose equivalent to an average dose of  $<20$  mg of prednisone daily for at least 4 weeks prior to the first dose of study agent.
9. if using immunosuppressive drugs within the past 6 months, must not have exceeded the following dose levels: methotrexate 25 mg/week, azathioprine 2mg/kg/day, mycophenolate mofetil (MMF) 3g/day, or mycophenolic acid (MPA) 1440mg/day.
10. if using immunosuppressive drugs, must be using not more than 1 immunosuppressive drug (does not account for antimalarials and glucocorticoids) and not have used any additional immunosuppressive drug within the past 3 months prior to the first dose of study agent.
11. must have laboratory test results within the following parameters:
  - a. Hemoglobin  $\geq 8.0$  g/dL (SI:  $\geq 80$  g/L)
  - b. White Blood Cells  $\geq 3.0 \times 10^3/\mu\text{L}$  (SI:  $\geq 3.0$  GI/L)
  - c. Neutrophils  $\geq 1.5 \times 10^3/\mu\text{L}$  (SI:  $\geq 1.5$  GI/L)
  - d. Platelets  $\geq 100 \times 10^3/\mu\text{L}$  (SI:  $\geq 100$  GI/L)
  - e. Serum creatinine  $\leq 2.0$  mg/dL (SI:  $\leq 177$   $\mu\text{mol/L}$ )
  - f. aspartate aminotransferase (AST) and alanine aminotransferase (ALT) levels must be within 2 x ULN range
12. must sign an informed consent form (ICF), indicating that he or she understands the purpose of, and procedures required for, the study and is willing to participate in the study.
13. all women of childbearing potential (WOCBP) must have a negative highly sensitive serum (beta-human chorionic gonadotropin [betahCG]) test at screening and a negative urine pregnancy test prior to first dose of study agent. Also, they must use a sufficient method of contraception (see section 5.3 PROHIBITIONS AND RESTRICTIONS).
14. a male participant must wear a condom with spermicidal foam/gel/film/cream/suppository when engaging in any activity that allows for passage of ejaculate to another person and must agree not to donate sperm for the purpose of reproduction during the study and for a minimum of 20 weeks after receiving the last dose of study intervention.
15. willing and able to adhere to the lifestyle restrictions specified in this protocol.

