### **Concomitant or previous medical therapies**

9. has received any live virus or bacterial vaccinations within 12 weeks prior to first study treatment or is expected to receive any live virus or bacterial vaccinations during the study or up to 20 weeks after last study treatment.
10. has received B cell depleting therapy within 12 months prior to first administration of the study agent (e.g. rituximab, ocrelizumab or obinutuzumab).
11. has received a therapy that inhibits B-cell activating factor (BAFF) (i.e. belimumab) within 3 months prior to first administration of the study agent.

12. has received prior experimental immunosuppressive biologic therapy for lupus (other than that described as allowed), less than 5 half-lives or 6 months, whichever is longer prior to first administration of the study agent.
13. has used oral or IV cyclophosphamide within 2 months prior to first administration of the study agent.
14. has ever been exposed to daratumumab or any anti-CD38 antibodies (e.g. TAK-079, MOR202, isatuximab).

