#### 6.4.1 GLUCOCORTICOID THERAPY

The use of glucocorticoids for the indication SLE is allowed to a maximum of 20mg daily prednisolone (or equivalent) throughout the study. The glucocorticoid dosage must be stable from baseline until Week 12 (primary endpoint study visit). After Week 12 (primary endpoint visit), it is possible to reduce the glucocorticoid dosage if the disease activity allows tapering, according to the judgment of the treating physician.

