#### 6.4.2 DISEASE-MODIFYING DRUGS

Background disease-modifying drugs must be continued throughout the study at stable doses even if participants achieve a state of low-disease activity (LLDAS) or remission, except for glucocorticoids, that are allowed to be tapered (see 6.4.1 GLUCOCORTICOID THERAPY). For the treatment of flares or ongoing disease activity, rescue medication is allowed according to section 6.5 RESCUE MEDICATION.

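### Section 5.1 requires a stable dose before entry for oral glucocorticoids only, so a recently started or raised sole immunosuppressant or antimalarial can add to the Week 12 change from baseline

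*Protocol*

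**What the plan says.** **Glucocorticoids.** Item 8 of protocol section 5.1 says a patient on oral corticosteroids "must be receiving this medication for at least 4 weeks and on a stable dose equivalent to an average dose of" less than 20 mg prednisone daily, for at least 4 weeks before the first dose. Section 6.4.1 adds an on-study rule: "The glucocorticoid dosage must be stable from baseline until Week 12 (primary endpoint study visit").

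**Immunosuppressants.** Item 9 sets a ceiling: "if using immunosuppressive drugs within the past 6 months, must not have exceeded the following dose levels", followed by maximum doses for methotrexate, azathioprine, MMF and MPA. Item 10 limits the number ("must be using not more than 1 immunosuppressive drug (does not account for antimalarials and glucocorticoids")) and requires that the patient "not have used any additional immunosuppressive drug within the past 3 months prior to the first dose of study agent". Neither item gives a minimum time on the permitted drug or a stable-dose period.

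**Antimalarials.** Item 10 leaves them out of the count, and no other entry criterion restricts their dose, duration or stability.

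**Washouts.** The exclusion criteria in section 5.2 cover B-cell depletion, BAFF inhibition, experimental biologics and cyclophosphamide ("has used oral or IV cyclophosphamide within 2 months prior to first administration of the study agent"). They do not cover the permitted drugs. Section 6.4 refers back to these criteria for pre-study therapy.

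**On study.** Section 6.4.2: "Background disease-modifying drugs must be continued throughout the study at stable doses". Section 6.5 allows additional disease-modifying drugs only from Week 12.

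**Population.** Section 4.3 describes moderate to severe disease "despite conventional treatment (e.g. immunosuppressants, antimalarial drugs, corticosteroids").

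**The concern.** The study is uncontrolled (section 4.1). The primary endpoint is the within-patient change in anti-dsDNA from baseline to Week 12 (3.2.1, 9.5.1), and SRI-4 is read at the same visit (9.5.2). An effect of a background drug that develops in those weeks therefore enters the result alongside any daratumumab effect.

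The protocol itself treats these drugs as capable of acting on the outcome:

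- Section 2.1.3 says plasmablasts and their immediate progenitors respond to immunosuppressive therapy, and that plasmablast expansion correlates with anti-dsDNA titres.
- Section 6.5 keeps additional disease-modifying drugs out until the primary endpoint visit.
- Section 7.3.4 counts new azathioprine, methotrexate or MMF for SLE activity towards a severe flare, and an added antimalarial towards a mild/moderate one.
- Section 8.2 classes a patient who starts a new permitted immunomodulator as a treatment failure.

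The same drug started as sole agent shortly before screening meets no such barrier. It also fits poorly with section 4.3, because a drug begun days earlier has hardly been tried. At stake is whether part of a Week 12 fall reflects a background change and not daratumumab.

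**Working it through.** **1. Text check: which rules constrain the period before the first dose?**

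| Drug | Minimum time on drug | Stable dose before first injection | Other entry limit | On-study rule |
|---|---|---|---|---|
| Oral glucocorticoid | at least 4 weeks (item 8) | at least 4 weeks (item 8) | average below 20 mg prednisone daily | stable baseline to Week 12 (6.4.1) |
| Permitted immunosuppressant | none | none | ceiling (item 9); one drug, no additional one in 3 months (item 10) | stable throughout the study (6.4.2) |
| Antimalarial | none | none | none | stable throughout the study (6.4.2) |

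Item 10 bars recent switches and add-ons. Three routes stay open: a sole immunosuppressant started recently, a dose raised recently within the ceiling, and an antimalarial started or raised recently. All three are open if the change falls just before screening. They are open during screening only if 6.4.2 is read as starting at baseline. Screening can be short: the synopsis says up to 4 weeks.

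**2. The plan's own figures.** Section 9.2 gives a mean reduction of 250 IE/ml with SD 121, about 50%. The effect size is 250/121 = 2.07, stated as 2.1. With 2.1, two-sided alpha 5% and the usual efficiency approximation for the signed-rank test, power at n = 5 is 91% (normal parent) or 85% (minimum efficiency); at n = 4 it is 75% or 65%. So 5 evaluable patients reproduces, and 5/(1 - 0.5) = 10 enrolled. The present point changes neither number.

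**3. Illustration of size.** The documents give no titre effect for a recent background change and no frequency of such patients. Both are assumed here.

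- Model: n = 10 and true daratumumab effect zero. The log ratio of Week 12 to baseline is normal with SD 0.3 or 0.5. In k of the 10 patients it is shifted by log(0.8) or log(0.6), a fall of 20% or 40%. There are 100,000 simulated trials per setting.
- Median change: 100 × (exp(mean of the sample median) - 1).
- Interval: the order-statistic (sign) interval for the median from the 2nd to the 9th value, coverage 1 - 2 × 11/1024 = 97.9%. It lies wholly below zero when at least 9 of 10 changes are negative, which has probability 11/1024 = 1.1% with no affected patients.

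| Affected patients | Median change | Interval wholly below zero |
|---|---|---|
| 0 of 10 | 0% | 1.1% |
| 1-2 of 10 | about -2% to -9% | about 1.4% to 3.2% |
| 3 of 10 | about -6% to -14% | about 2% to 5% |
| 5 of 10 | about -11% to -23% | about 4% to 16% |

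**4. Cross-check on the raw scale.** A fall of 250 IE/ml that is about 50% implies a baseline near 500 IE/ml. With a smaller assumed fall of 10-30% in 2 of 10 patients, the mean decline is 0.2 × 0.10 × 500 = 10 to 0.2 × 0.30 × 500 = 30 IE/ml. That is 10/250 = 4% to 30/250 = 12% of the planned effect.

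**The case against.** **Section 6.4.2 may already reach into screening.** Sections 1.5 and 4.4 count the 4 screening weeks in the study duration, and 6.4.2 says throughout the study, whereas 6.4.1 says from baseline where that is meant. On this reading an increase during screening breaches 6.4.2, and a new immunosuppressant may also meet the ban on additional agents in 5.4 and 6.6. This stands as a reasonable reading. A reader might infer that a mid-screening increase is plainly allowed; the text does not settle that. A change just before screening stays open either way.

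**The open route is narrow.** Item 10 stops switches and add-ons, item 7 requires at least two earlier drugs to have failed or not been tolerated, and 4.3 steers the single site away from patients whose new drug is untested. This also stands, and makes a small number of affected patients more plausible than a large one. But item 7 does not date the current drug, and 4.3 is a description, not an eligibility criterion.

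**The size is assumed.** Correct. A reader might infer from the 5-of-10 row that nearly half the planning effect could be an artefact (about 23% against 50%). That needs a 40% fall in half the patients together with no daratumumab effect, and nothing in the documents supports that combination.

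**The study is exploratory.** Section 9.5.1 plans no confirmatory test and the objective speaks of association, so a false-positive framing carries little weight. The reported median change would still be shifted.

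**The effect can be examined afterwards.** A reader might infer that it can never be separated. That goes too far: section 9.1.6 already plans summaries of prior and concomitant SLE medication, so results with and without such patients can be shown, though imprecisely.

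**Conclusion.** The gap is real on the text. Entry requires dose stability for glucocorticoids but does not date the start or last change of the one permitted immunosuppressant, and it sets no rule for antimalarials. Neither the washouts, section 6.4.2 nor section 6.5 stops a start or increase shortly before screening, and 6.4.2 then carries the drug through the primary endpoint visit.

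The consequence is a possible shift of the Week 12 change towards benefit, of unknown size. The illustrative shifts with 1-3 affected patients are well below the planning effect, and they rest wholly on the assumed 20-40% fall, the assumed number affected, a zero daratumumab effect and a log-ratio SD of 0.3-0.5. Bias arises only if such patients are enrolled.

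A reader might take this as a flaw that invalidates the primary analysis. The documents do not support that: no stated figure is wrong, the sample size is unaffected and the analysis is descriptive. It is a change that should be made because it is cheap, not one on which the study stands or falls.

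**What to change.** 1. Reconcile items 9 and 10 of section 5.1, and section 6.4.2, with item 8. Add a stability requirement before the first dose for the permitted immunosuppressant and for antimalarials. Its length is for the sponsor to set and justify. Carry the same wording into the synopsis.
2. State in 6.4.2 whether the stable-dose rule runs from screening or from baseline.
3. If enrolment has begun, record the start date and last dose-change date of each background drug. Report the primary endpoint and Week 12 SRI-4 with and without patients whose background drug changed recently, with that window fixed in advance.

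**Cost.** Items 1 and 2 need a few lines in an amendment, and a few candidates wait or are rescreened, which section 5 already permits. Item 3 is one extra analysis of medication data already being collected, provided the dates are captured. With 10 patients, or 5 evaluable under the plan's own drop-out assumption, the with/without comparison will be imprecise and should be presented as descriptive.

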## 5.2 EXCLUSION CRITERIA OF THE CORE STUDY PERIOD

Any potential participant who meets any of the following criteria will be excluded from participating in the study:

### **Coexisting medical conditions or past medical history**

1. has any unstable or progressive manifestation of SLE (lupus cerebritis, optic neuritis, transverse myelitis, psychosis, uncontrolled seizures, systemic vasculitis, end-stage renal disease, rapidly progressive Class III or IV glomerulonephritis, isolated Class V lupus nephritis [i.e. without coexistent Class I, II, III, or IV nephritis], Class VI lupus nephritis, pulmonary hemorrhage, myocarditis) that is likely to warrant escalation in therapy beyond permitted background medications. Subjects requiring renal hemodialysis or peritoneal dialysis are also excluded.
2. has or has had a history of any clinically significant medical illness, or medical disorders the investigator considers significant should exclude the participant, including (but not limited to), hematological disease, immune deficiency states, respiratory disease, cardiovascular disease (including poor peripheral venous access), hepatic or gastrointestinal (GI) disease, neurological or psychiatric disease, ophthalmological disorders, neoplastic disease, renal or urinary tract diseases, or dermatological disease.
3. has or has had a serious infection (e.g. sepsis, pneumonia, or pyelonephritis), or been hospitalized or received IV antibiotics for a serious infection during the 3 months prior to consent.
4. had major surgery, (e.g. requiring general anesthesia) within 3 months before screening.
5. has or has had an acute illness, including a common cold, within 2 weeks prior to first study treatment or has had a major illness or hospitalization within 3 months prior to consent.
6. has other inflammatory diseases that might confound the evaluations of efficacy, including but not limited to rheumatoid arthritis (RA), psoriatic arthritis.
7. has received, is known to have received, or is suspected to have an intolerance or hypersensitivity (including delayed-type hypersensitivity) to any monoclonal antibodies or antibody fragments, is known to have allergies or clinically significant reactions to human proteins, monoclonal antibodies, or antibody fragments, or to any components of the formulation used in this study, including daratumumab.
8. has a history of drug or alcohol abuse according to Diagnostic and Statistical Manual of Mental Disorders (5th edition) (DSM-V) criteria within 1 year before consent or positive test result(s) for alcohol or drugs of abuse (including barbiturates, opiates, cocaine, cannabinoids, amphetamines and benzodiazepines that were not prescribed as part of routine medical care) at Screening.

